1. **Conduct a randomized controlled trial assigning worksites in a 2:1 ratio to a multiple-program health intervention or a wait-listed control.** The multiple-program intervention will be a combination of the Human Performance Institute (HPI) intervention and iDiet, a behavioral weight loss program, with randomization to either partial provided food or a gift card for self-selection of food. Within worksites, employees will be eligible to select either the HPI intervention or the behavioral intervention. **Primary outcomes will be quality of life and energy levels (HPI participants and controls) and weight (weight loss intervention participants) at 6-18 months.** Secondary outcomes include cardiometabolic risk factors.
2. *The HPI working hypothesis* is that enrollment in the HPI intervention will result in significant improvements in quality of life (primary outcome) and energy levels compared to controls over 6 months and no significant decrease in quality of life during the subsequent 12-month period in the intervention participants. Exploratory outcomes also tested will include body weight and fat, fasting blood glucose, a lipid panel and systolic and diastolic blood pressure.
3. *The behavioral weight loss program working hypothesis is that* iDiet participants receiving gift card will lose weight over the first 6 months compared to weight listed controls and will lose weight compared to baseline over 18 months. In addition, iDiet participants receiving the ready-prepared foods will lose more weight over 18 months compared to participants receiving gift cards.
4. An exploratory hypothesis is that greater weight loss will be associated with reduced levels of hunger and food cravings and increased satiety.
5. **Background and Rationale**
   1. Background

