The increase in vitality score in the intervention worksites compared to controls is expected to be 9 points at both time points compared to the control. Since randomization is at the worksite level, the total variance includes both the within worksite and between worksite variance. Based on a within worksite standard deviation of 15 and 20 people per worksite and a between worksite standard deviation of at most 3.4, 12 worksites with a 2:1 worksite allocation in favor of treatment are needed to have 80% power to detect an expected increase in vitality score of 9 points.

For the participants electing to participate in the behavioral weight loss program, randomization to either with provided Yevo foods or a gift card such that one half of the participants are in one group and the other half will be assigned to the remaining arm.. Assuming worksite is a fixed variable, 8 worksites with 30 subjects each (240 total subjects) is at least 80% powered to detect a 2.4% difference in weight loss with provided food compared to gift cards assuming no diet by food interaction. If there is a significant food by diet interaction, the study will have an 80% power to detect an interaction that is a 4.5% difference in weight change with provided food for iDiet and 3% improvement in diet.

Data analyses will be performed using the latest version of SAS for Windows, currently 9.4 (Cary, NC: SAS Institute Inc.). All testing will be two-sided and results will be judged statistically significant if the observed significance level (P value) is <0.05. Data will be examined graphically and numerically for outliers and other aberrations that might lead to misleading results. Data may be transformed prior to formal analysis if necessary to fit the assumptions for the statistical model to be employed. Both studies (HPI intervention and the iDiet intervention) will be analyzed according to Intention-To-Treat principles to best reflect what happens when individuals start one of the interventions. If necessary, missing data will be estimated using multiple imputations using the MI Procedure of SAS for Windows.

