For the HPI intervention in whom those randomized to intervention will be compared primarily with subjects at control sites who elected the HPI intervention prior to workplace randomization, a mixed linear model with worksite nested within the randomization to HPI intervention or control as a random factor will be use to assess the effect of the intervention on change in vitality scale score. Baseline vitality score, weight, ethnicity and gender will be included as covariates.

The diet intervention will compare those receiving the iDiet with a primary outcome of percent change in weight at 6 and 18 months. To assess the effect of diet and food delivery method, a multi-factor model with diet, food and worksite as independent variables will be used, controlling for baseline weight, gender and ethnicity. Interactions between diet and worksite, food and worksite and food and diet will be assessed and included in the final model if significant. Change in weight for the HPI intervention andchange in vitality score for those in the diet intervention will be included as secondary outcomes.

Secondary analyses will include a comparison of the 3 intervention arms (with and without provided food for the iDiet) as well as the combined effect of intervention on change in anthropometric measures including body fat, and also lipids, blood glucose levels and blood pressure using the same models described above adjusting for the appropriate baseline values. Additionally, regression models will be used to assess the effect of different adherence metrics, activity levels, appetite regulation (hunger and food cravings) and measures of wellbeing on outcome measurements both within and between intervention groups for each arm of the study. In addition, predictors of changes in cardiometabolic parameters will be examined. Prior to enrollment of subjects, a formal data analysis plan will be prepared and submitted as part of clinical trial registration.

1. **Worksite Characteristics**

A convenient sample of worksites in the Greater Boston area, consisting of worksites which have previously expressed interest, and respond to the recruitment letters will be invited to participate in the Worksite Wellness Study. The first twelve eligible worksites with a higher employee interest in worksite wellness will then be invited to enroll in the study.

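### Interaction tests on the weight data decide the final model for provided food versus gift card, and the protocol does not say which food effect then answers the hypothesis

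*Protocol*

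**What the plan says.** Under Aim and Hypotheses, the protocol states one directional hypothesis for the food randomisation: "iDiet participants receiving the ready-prepared foods will lose more weight over 18 months compared to participants receiving gift cards".

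The section on sample size and statistical analyses sets the analysis of the "primary outcome of percent change in weight at 6 and 18 months". The starting point is "a multi-factor model with diet, food and worksite as independent variables will be used, controlling for baseline weight, gender and ethnicity". The next sentence is the selection rule: "Interactions between diet and worksite, food and worksite and food and diet will be assessed and included in the final model if significant". No separate level is given for these tests, so the general rule applies: "All testing will be two-sided and results will be judged statistically significant if the observed significance level (P value) is <0.05".

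The power statement in the same section reads "8 worksites with 30 subjects each (240 total subjects) is at least 80% powered to detect a 2.4% difference in weight loss". It takes worksite as fixed and is conditional on diet and food not interacting. A second statement gives a different detectable target for the case in which the food-by-diet interaction is significant. The section also promises a formal data analysis plan before enrollment. That plan is not at hand.

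**The concern.** The hypothesis asks for one number: the overall difference in weight change between provided food and gift card. In the additive model, that number is the food effect. Under the selection rule, the model that supplies it is known only after the outcome data have been tested.

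Food is randomised among iDiet participants within each of the eight intervention worksites, so food by worksite can be estimated. Once it is in the model with worksite fixed, there are eight food effects. The hypothesis could then be answered by their equal-weight average, an average weighted by site size, a set of site-specific results, or the coefficient at whichever site the software uses as reference. These are different quantities with different precision, and the protocol does not choose among them.

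The rule applies at both 6 and 18 months, so the food effect could be defined differently at the two time points. The other two listed interactions involve diet. Among iDiet participants, diet has a single level, so those terms cannot be estimated. That mismatch needs its own correction, and the present point does not rest on it.

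**Working it through.** **Inputs from the protocol:** 8 worksites of 30 (240 in total), 1:1 food to gift card, hence 120 per arm and about 15 versus 15 per site; difference 2.4 points; power at least 80%; two-sided 0.05; worksite fixed.

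**Assumptions, because the protocol gives no figure:** the SD of percent weight change, equal site sizes, no dropout, and the true between-site SD of the food effect (τ), taken as 0, 1.5, 2 and 3 points.

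1. *Stated power.* It cannot be reproduced without an SD, so solve for the SD: 2.4 / [(1.960 + 0.842) × √(2/120)] = 6.64 points, or 6.61 with the t distribution on 231 df. Because the protocol says at least 80%, this is an upper bound if all 240 are analysed. For comparison, power would be 96% at SD 5, 87% at 6, 76% at 7 and 64% at 8.

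2. *Precision of the candidate food effects (SD 6.61).*
   - Overall effect: 6.61 × √(2/120) = 0.85 points.
   - One site: 6.61 × √(2/15) = 2.41 points.

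3. *How often the rule adds food by worksite.* The F test has 8 − 1 = 7 and 240 − 16 = 224 df, with critical value 2.05. A site's food difference has sampling variance 2 × 6.61²/15 = 5.83. True variation multiplies the F statistic by 1 + τ²/5.83, so the inclusion probability is P(F > 2.05 / [1 + τ²/5.83]):
   - τ = 0: P(F > 2.05) = 5%
   - τ = 1.5: P(F > 1.48) = 18%
   - τ = 2: P(F > 1.22) = about 30%
   - τ = 3: P(F > 0.81) = 58%

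4. *Effect on the food test (true mean difference 2.4, equal sites, simulated).*

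| τ | Additive model fixed in advance | Rule, site effects averaged | Rule, reference-site coefficient |
|---|---|---|---|
| 0 | 80% | 80% | 78% |
| 1.5 | 76% | 76% | 68% |
| 3 | 69% | 70% | 50% |

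   At τ = 2, a run of 5,000 trials with SD 6.64 gave 72% for the fixed additive model and 60% for the rule with the reference-site coefficient.

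   Hand check of the first column: the estimate has SD √(0.853² + τ²/8), which is 0.853, 1.005 and 1.361. The margin over the critical value is 2.4 − 1.97 × 0.853 = 0.72. This gives about 80%, 76% and 70%.

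5. *Type I error with no true variation.* It stays at 5.0% if the site effects are averaged. In a run of 5,000 trials it moved from 4.7% to 5.4% with the reference-site coefficient.

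6. *Unequal sites.* The experimental design section allows small adjustments to enrolment per site. With an assumed and rather wide spread of 16 to 46 people, the additive estimate and the equal-weight site average differ by 0.23 to 0.37 points on average. The overall power of the two-stage rule with averaging still moves by less than 1 point (for example 78.7% to 78.4% at τ = 0).

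**The case against.** The strongest reply is that the loss of power requires a reading the protocol never states. It does not mention a reference-site coefficient. With effect coding or site-averaged contrasts, the food effect in the interaction model is again an average over sites. With equal sites it is then the same estimate as in the additive model. This stands, and it removes any claim that power must fall or that type I error is seriously inflated.

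It can also be said that the rule is itself written in advance, with named factors and covariates, and that the summary of the food effect could be settled in the promised analysis plan. This stands in part. The protocol does plan something, and the unseen plan may name the summary. But the protocol's sentence is an explicit rule on the primary model, and an analysis plan could fix the additive model only by departing from that sentence.

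Three stronger readings are tempting, and the documents do not support them:

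- A reader might take the one-site power as the power in trials where the interaction is kept: 2.4/2.41 = 0.996, and P(Z > 1.96 − 0.996) is about 17%. That figure ignores the selection. Given a significant interaction test and no true variation, the reference-site contrast rejects in about 30% of trials. This agrees with the overall figure: 0.95 × 80% + 0.05 × 30% = 77.5%.
- A reader might infer that the rule alters the model mainly at random. The inclusion rate rises from 5% to 58% as true variation grows, so the test responds to real variation, although it often misses moderate amounts.
- A reader might infer that the 80% power was stated for a model free of all interactions. The text conditions only on there being no diet-by-food interaction and does not mention food by worksite.

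**Conclusion.** The point holds in a limited form. The protocol lets tests on the outcome data choose the final model for a primary comparison and does not define the food effect that answers the hypothesis once food by worksite is retained. On the assumptions above, this would happen in 5% of trials if the food effect is the same everywhere, and in about 18% to 58% if it varies between sites by an SD of 1.5 to 3 points.

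The consequence that follows from the text is an estimand that depends on the data, possibly differing between 6 and 18 months. A loss of power is conditional. It is negligible if equal sites are averaged. If a reference-site coefficient is read, it runs from 2 points (80% to 78%) to 19 points (69% to 50%). Type I error is little affected with no true variation.

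The SD of 6.6 is back-solved, and the between-site SDs are assumptions without support in the protocol. The conclusion about the undefined estimand does not depend on either.

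**What to change.** Replace the interaction-selection sentence with a fixed specification along these lines: *The primary model for percent weight change contains food, worksite, baseline weight, gender and ethnicity. No interaction is added on the basis of its significance. The overall food effect from this model at 18 months answers the provided-food hypothesis, whatever the interaction test shows. The same model is used at 6 months. Variation of the food effect between worksites is reported separately as a heterogeneity analysis, with an estimate and confidence interval.*

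The diet factor and the diet interactions in the same paragraph should be reconciled with the single-diet design at the same time. The formal analysis plan should carry the same wording. The cost is one sentence in each document, with no new data and no change in sample size.

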The interventions that are to be used in this study are all long-term group behavioral wellness programs, and implementing them simultaneously allows for a combined evaluation of these programs for concurrent use in the workplace. The combination of the 2 programs is anticipated to be highly acceptable to worksites because they are commercially available for large scale dissemination and delivery in a group format. It is anticipated that both of these programs may be beneficial in affecting wellness..

- 1. Rationale

The rationale for these technical objectives is that there is an urgent need for sustainable worksite wellness interventions generally, and two successful programs designed to achieve worksite wellness and improvements in employee health are being tested for sustainability in this long term study. Preliminary data suggests that HPI may be particularly effective in improving overall energy, as well as general and mental health, while our prototype iDiet intervention may be particularly effective and sustainable for long-term improvements in weight. Furthermore, the provision of foods for a subset of participants in the iDiet arm may facilitate adherence and overall weight control, suggesting that provided foods offer an important adjunct to enhance effectiveness of worksite weight loss programs. By conducting a comparison of the more specific dietary composition profiles in the iDiet to the energy maintenance focus of the HPI intervention we will be evaluating current best practices for an extended period of time (18 months) at worksites. The intention is to help all employees and worksites participating in this research program and to identify the most optimal long term approach to wellness, involving dietary and exercise recommendations as well as particular food provisions necessary for sustainable health. Once the results of this study are available, the most effective long-term approach to health and wellness/weight control can then be used for scaling practical, effective programs for worksite wellness.

1. **Research Plan**

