         3. Willingness to provide release from his/her physician before starting the intervention program-a requirement for each of the 3 wellness programs which can be faxed to [name], or emailed to [[contact]](mailto:[contact]) or mailed back to the HNRCA at [name].
         4. Willingness to provide email ID and contact information to the commercial program facilitators to receive program materials and other feedback related to program progress.
         5. Willingness to complete outcome assessments and self-monitoring in order to track intervention effectiveness
         6. BMI ≥ 20 kg/m^2^ and < 50 kg/m^2^ at screening, if participant opts into the HPI arm
         7. BMI ≥ 25 kg/m^2^ and < 50 kg/m^2^ at screening, if participant opts into the weight loss arm
      2. Exclusion criteria:
         1. Employees who are temporary contract workers or employees who work remotely most of the time
         2. < 21 years of age
         3. Participation in a weight loss program or intensive wellbeing program at time of enrollment
         4. Pregnant or lactating (per self-reports, now or intended during study)
         5. Prior weight loss surgery or a medical complication that would prevent full participation
         6. Multiple severe dietary intolerances (e.g. gluten combined with dairy or meat) which would reduce intervention adherence
         7. Non-English speaking
         8. Individuals who have lost > 15 pounds in the past 6 months
         9. mobility limitations (inhibiting the ability to stand on one’s own or get on and off of the scale)
         10. Major diseases including active cancer or cardiovascular disease
         11. BMI < 25 kg/m^2^ or ≥ 50 kg/m^2^ at screening, for those that opt-in to the weight-loss group
         12. BMI <20 kg/m^2^ or ≥ 50 kg/m^2^ at screening, for those that opt-in to the HPI group

For those interested in the weight loss intervention, additional exclusion criteria are as follows:

1. Any condition that influences the ability to absorb food (e.g. inflammatory bowel disease or celiac disease)
2. Very active individuals (> 2 hours/day or >14 hours/week of vigorous activity).

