Those interested in participating will be screened on **Recruitment** Day. They will first be administered the screening ICF, and the screening will involve a questionnaire on exclusions and measurements of weight and height for calculation of BMI and the option to choose the diet or the HPI arm of the intervention. If the individual is eligible they will then be administered with the informed consent form (ICF) for baseline assessments. The **Recruitment** Days, screening and baseline measurements will be conducted by members of the Tufts team (study coordinators, research staff and investigators) depending on availability.

Randomization of worksites to the intervention or control condition will be done following the completion of baseline assessments. Once worksites are randomized to receive the intervention or weight-listed control condition, participants within the intervention worksite will be assigned to the intervention arm that they opted into at screening i.e. HPI or diet arm. However, those who had expressed an interest in the

iDiet will be further randomized to receive Yevo foods or a gift card. Once randomization has occurred, participants will be given the consent form to read and sign prior to enrollment in the study.

Any questions or concerns will be addressed by a study team member prior to signing of the ICF. Copies of the signed ICF will be given to the study participants. Enrollment of all participating sites and employees will occur over a 6 month period during the first year.

1. **Transportation:** No transportation will be provided for this study since all support and assessments are provided and conducted in the workplace.
2. **Informed consent process:** Eligibility for inclusion of a worksite is multistep and is summarized in the protocol (Section III, parts C and D).
   - 1. Informed Consent for Initial Web Survey For All Employees at Worksite
     2. HR Company Agreement Form
     3. Informed Consent for Worksite **Recruitment** Day and Screening
     4. Informed Consent for Baseline Assessments For All Employees who have expressed an interest to join an intervention group at Worksite
     5. Informed Consent for:
3. iDiet Intervention
4. Human Performance Institute Intervention
5. Control group

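### HPI versus iDiet is a choice made by participants under different eligibility rules, so the planned three-arm comparison cannot show which programme works better

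*Protocol*

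**What the plan says.** All references are to the Protocol.

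- **How the programme is assigned.** Aim and Hypotheses, item 1: "Within worksites, employees will be eligible to select either the HPI intervention or the behavioral intervention". Screening Interview/Questionnaire: once worksites are randomised, "participants within the intervention worksite will be assigned to the intervention arm that they opted into at screening".
- **What is randomised.** Worksites are randomised 2:1 to intervention or wait-list. Within iDiet, participants are randomised to Yevo foods or gift card.
- **Who may enter.** Subject Characteristics sets "BMI ≥ 20 kg/m^2^ and < 50 kg/m^2^ at screening, if participant opts into the HPI arm" and "BMI ≥ 25 kg/m^2^ and < 50 kg/m^2^ at screening, if participant opts into the weight loss arm". Two exclusions apply to the weight-loss programme only: conditions that affect food absorption, and "Very active individuals (> 2 hours/day or >14 hours/week of vigorous activity").
- **What is compared.** Sample size and statistical analyses: "Secondary analyses will include a comparison of the 3 intervention arms (with and without provided food for the iDiet"). This reuses the models set out just before it, with baseline values of each outcome. Those models carry baseline weight, gender and ethnicity. The Outcomes section adds t-tests of overall means between interventions and names no covariates.
- **What it is for.** Rationale: "By conducting a comparison of the more specific dietary composition profiles in the iDiet to the energy maintenance focus of the HPI intervention", the investigators expect to evaluate current best practice, identify the best long-term approach and take it to scale.

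None of these sections marks the HPI–iDiet contrast as non-randomised.

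**The concern.** People who want to lose weight and people who want more energy at work are likely to differ in motivation, health and expected course before either programme starts. The eligibility rules add a structural difference. A gap between HPI and iDiet in weight, vitality or cardiometabolic change would then mix what the programmes do with who chose them.

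The protocol recognises this for its primary HPI analysis, where HPI participants are compared with control-site people who had elected HPI before worksite randomisation. It does not carry that logic over to the comparison between programmes. At stake is the recommendation about which programme to scale up, which would appear to come from a randomised trial when that particular contrast does not.

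**Working it through.** **1. The plan's own figure.** The three-arm comparison has no stated power. The one stated power with full inputs is for vitality, HPI versus control: 80% for 9 points, 8 versus 4 worksites, 20 people per site, within-site SD 15, between-site SD 3.4.
- Variance of a site mean = 3.4² + 15²/20 = 22.81.
- SE = √(22.81 × (1/8 + 1/4)) = 2.925.
- A noncentral t with 10 df, two-sided 0.05, gives 79.2%.

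The figure reproduces. The present point does not depend on it.

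**2. The contrasts.**

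| Contrast | Assigned by | Same eligibility? |
|---|---|---|
| iDiet + food vs iDiet + gift card | Randomisation of individuals | Yes |
| HPI vs iDiet + food | Participant's choice | No |
| HPI vs iDiet + gift card | Participant's choice | No |

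**3. What adjustment can do.** Baseline outcome value, weight, gender and ethnicity reduce measured imbalance. They do not capture the reason for choosing a programme. Between BMI 20 and 25 there are no iDiet participants, so in that range a model can only extrapolate. For illustration, assume that employee BMI is normal with mean 27 to 31 and SD 5 to 7, and that the two programmes differ only by their floors. Mean BMI is then 0.9 to 2.4 kg/m² higher in iDiet, and about 10% to 29% of HPI participants lie below 25. The BMI distribution is an assumption; the documents give none.

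**4. What a residual bias would do to a test.** The food comparison (2.4%, 120 per group, 80% power) implies an SD of 2.4 / ((1.96 + 0.84) × √(2/120)) ≈ 6.6 percentage points of weight. Planned numbers at 8 sites are 8 × 20 = 160 HPI and 8 × 30 = 240 iDiet, so SE = 6.6 × √(1/160 + 1/240) ≈ 0.67. With no true programme difference, the nominal 5% test rejects as follows:

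| Assumed residual bias (percentage points) | Rejection rate |
|---|---|
| 0 | 5% |
| 1 | 32% |
| 2 | 84% |
| 3 | 99% |

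The bias values are assumed and clustering is ignored. The table shows sensitivity, not an estimate of the bias.

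**5. Can the design do better?** Yes, up to 6 months. Choice is recorded at screening, before worksite randomisation. Tables 1 and 2 list control participants as future HPI and iDiet groups, with weight and SF-36 at time points 0, 3 and 6. The plan has 200 controls at 4 sites, 50 per site. If the 20/30 split holds there (an assumption), that gives 4 × 20 = 80 HPI electors and 4 × 30 = 120 iDiet electors. After 6 months controls join a programme, so no untreated comparison remains.

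**6. What it costs in precision.** Take within-site SD 15 for vitality, and site effects that are common to both programmes and therefore cancel.
- Direct HPI–iDiet difference: SE = 15 × √(1/160 + 1/240) = 1.53.
- Difference between the two controlled effects: SE = 15 × √(1/160 + 1/240 + 1/80 + 1/120) = 2.65.
- Variance ratio: 0.03125 / 0.010417 = 3.0.
- Difference detectable with 80% power (2.80 × SE): about 4.3 versus 7.4 points.

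**The case against.** The strongest reply is that this is one secondary sentence plus background language. The primary outcomes differ by programme (vitality for HPI, weight for iDiet), so the confirmatory design is not a contest between them. The Background also presents the programmes as complementary. The models to be reused are not written with an HPI-versus-iDiet term, and a formal analysis plan is promised, so the exact contrast may be set there. This stands as a limit on scope. It does not dispose of the point, because the three-arm comparison and its stated purpose are fixed in the protocol.

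The t-tests between interventions could include food versus gift card, which is randomised. That also stands: only their use for HPI versus iDiet is at fault.

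The remedy has real limits. Variance triples. By mean squared error, the direct contrast is better at an assumed bias of 1 to 2 points (1.53² + 1² = 3.3 and 1.53² + 2² = 6.3, against 2.65² = 7.0). Nor does the controlled difference remove effect modification: each effect belongs to its own electors. Both points stand, and they are reasons to keep the contrast descriptive. The direct contrast has a tighter interval around a quantity that includes an unknown bias.

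A reader might infer that the direct contrast is wrong by the whole difference in untreated course between the two kinds of elector. That could apply only to the unadjusted t-tests; in the adjusted models only the residual part remains. A reader might also express an assumed bias as a share of the 9-point vitality effect. That effect is for HPI versus control, and the protocol states no expected HPI–iDiet difference, so such a percentage would measure nothing in the contrast at issue.

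**Conclusion.** The point holds for HPI versus iDiet only. That contrast is self-selected under different eligibility rules, the planned covariates cannot be relied on to remove the confounding, and there is no overlap at BMI 20 to below 25. It therefore cannot support a conclusion about the better programme. The direction and size of the residual bias cannot be derived from the documents; the rejection rates and BMI figures above rest on stated assumptions.

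It would go too far to read this as a fault in the trial's main inference. HPI participants are compared with like electors at control sites, and food versus gift card is randomised. It would also go too far to say that the control electors fully solve the problem: they remove differences in untreated course up to 6 months, but the two effects still describe different populations.

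**What to change.** In Sample size and statistical analyses and in Outcomes:

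- Keep food versus gift card as the only randomised head-to-head test among the intervention arms.
- At 6 months, report each programme's effect against control-site participants who elected the same programme, with worksite as a random factor. This extends to iDiet what is already planned for HPI, and it fits the existing iDiet hypothesis, which is framed against wait-listed controls.
- Label any HPI–iDiet contrast as non-randomised and descriptive. At 6 months give it as the difference between those two effects with a confidence interval. Add a sensitivity analysis restricted to people who meet both programmes' eligibility criteria.
- At 12 and 18 months show the programmes side by side only.
- Do not use unadjusted t-tests for HPI versus iDiet.

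In the Rationale, reword the aim so that the conclusion about the best approach does not rest on this contrast.

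The cost is wording. The main controlled estimates need no new data. The restricted analysis needs the iDiet-only exclusions to be recorded for HPI electors too, which should be confirmed against the screening questionnaire. The statistical cost is the loss of precision shown above.
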